### Interim analyses and stopping guidance

A Data and Safety Monitoring Board (DSMB) will be appointed and act according to a charter agreed by the investigators and approved by the sponsor. Six months after the recruitment of the last patient, an interim analysis, based on the ITT population, will be performed to evaluate the continuation of the trial. As main statistical measures, an O’Brien-Fleming plot of the primary endpoint and mortality (calculating *Z*-scores) will be performed. The interim analysis will be performed and presented by a sub-investigator not otherwise involved in the data collection or analyses, overlooked by the trial statistician. The data will be presented in a blinded fashion.

At the interim analysis, the event rate and effect size for the primary endpoint, as well as the safety and progress of the study, will be assessed by the DSMB, and follow-up duration may be adjusted accordingly. Safety will be assessed by comparing event rates to the event rate presumption used for the initial sample size determination. The study may stop for futility if it is deemed improbable to achieve a follow-up duration sufficient to detect a clinically important effect size. The study will not stop for superior efficacy at interim analysis. We wish to prioritize increasing the likelihood of having sufficient power to conclude on the secondary endpoints at the final analysis.

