### Outcomes

The primary efficacy endpoint is the occurrence of hospitalization requiring AECOPD or death from all causes within 12 months. Secondary efficacy endpoints included (i) moderate COPD exacerbations; (ii) all-cause hospitalization; (iii) ICU admission; (iv) need for non-invasive ventilation; (v) all-cause mortality; (vi) SABA use/pick-up rate; and exploratory endpoints (i) relation between adherence and AECOPD hospitalization, (ii) change in CAT score, (iii) change in MRC score, and (iv) change in “soundly sleeping” parameter of CAT.

The details on the primary and secondary outcomes of the study can be seen in Tables 1, 2, and exploratory outcomes in Table 3.

**Table 2 tab2:** Secondary and exploratory endpoint definition.

Endpoint	ICD-10/ATC codes	Inpatient/outpatient/minimum required length of stay/other criteria
Moderate COPD exacerbations	Prednisolone: H02AB06 or Antibiotics: J01CA04, J01AA02, J01CR02, J01MA14	Excluding hospitalizations and emergency room visits: DJ441 (A)
Hospitalization (all-cause)		Inpatient, length of stay ≥24 h
Hospitalization in ICU (all-cause)		Inpatient, ICU, length of stay ≥24 h
Need for NIV	BGDA1	A or B
Mortality (all-cause)		Participant registered as dead in the CPR register.
SABA use/pick-up rate	R03AC02, R03CC02, R03AC03	Danish National Prescription Registry
Change in CAT score	Questionnaire	At 6 and 12 months
Change in MRC score	Questionnaire	At 6 and 12 months

The time frame is ≥1 day after randomization until the end of the study (12 months from randomization) for all outcomes. A = primary discharge diagnosis and B = secondary discharge diagnosis. COPD, chronic obstructive pulmonary disease; ICU, intensive care unit; NIV, non-invasive ventilation; CPR, Central (National) Person Registry; SABA, short-acting beta-2 agonists; CAT, COPD assessment test.

**Table 3 tab3:** Exploratory endpoint definition.

Endpoint	Data source or ICD-10 codes	Inpatient/outpatient/minimum required length of stay/other criteria
Relation between adherence and hospitalization-requiring AECOPD	Questionnaire, DJ440, DJ441	For hospitalizations: Type A diagnosis (primary discharge diagnosis). Inpatient and length of stay ≥24 h, or emergency room visits. Deaths excluded.
Change in CAT score	Questionnaire	At 6 and 12 months
Change in MRC score	Questionnaire	At 6 and 12 months
Change in CAT “soundly sleeping” parameter	Questionnaire	At 6 and 12 months

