### Sample size

In Denmark, approximately 400,000 people are assumed to have COPD; however, approximately a quarter of them have not been diagnosed yet. We have data showing that 178,000 citizens have collected LAMA medication within the last 6 months. At the same time, we know that every year, there are approximately 20,000 admissions with AECOPD (severe AECOPD) and 6,000 deaths in patients with COPD. Assuming 50% of the AECOPD admissions are either unique or preceding a death, there are 16,000 annual events corresponding to our primary outcome. Thus, the annual risk of a primary outcome is approx. 16,000/178,000 = 8.9%. We hypothesize that evening LAMA administration will reduce the relative risk of the primary outcome by 25%, corresponding to a 2.2% absolute risk reduction. Assuming 84.4% uniformly distributed adherence to the intervention (= approximately 1 in 6 does not adhere), this corresponds to a relative risk reduction of 21.3% = 1.9% absolute risk reduction (average effect among all) in the ITT population. Alpha and power (1-beta) are set at 0.05 (two-sided) and 0.8, respectively. This leads to a needed sample size of 6,662 (3,331 + 3,331).

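### The interim safety sentence uses the planning event rate as comparator instead of the morning arm, and effect-informed changes to follow-up conflict with the fixed 12-month endpoint

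*Protocol article*

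**What the plan says.** All references are to the protocol article.

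**Safety at the interim.** *Interim analyses and stopping guidance* plans one look, six months after the last patient is recruited, in the ITT population. Its main measures are an O'Brien-Fleming plot and Z-scores for the primary endpoint and for mortality. Its safety sentence is: "Safety will be assessed by comparing event rates to the event rate presumption used for the initial sample size determination". *Sample size* gives that presumption: "the annual risk of a primary outcome is approx. 16,000/178,000 = 8.9"%. The 16,000 rests on a further assumption: "Assuming 50% of the AECOPD admissions are either unique or preceding a death". Morning administration is named as the control under *Explanation for the choice of comparators*.

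**Follow-up.** The same interim section says that the event rate, effect size, safety and progress "will be assessed by the DSMB, and follow-up duration may be adjusted accordingly". It describes futility in terms of whether a long enough follow-up can be achieved, and it rules out stopping for efficacy.

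**Endpoint and final test.** *Outcomes* says: "The primary efficacy endpoint is the occurrence of hospitalization requiring AECOPD or death from all causes within 12 months". *Trial design* and the note to Table 1 also give 12 months, and the note to Table 2 applies it to all its outcomes. The two statistical-methods sections keep significance at p<0.05, two-sided.

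**The concern.** **Safety comparator.** A planning rate exists to size a trial. It is not a control group. If the enrolled population has a lower risk than presumed, an evening arm that is worse than morning can still match the presumption. If the population has a higher risk, both arms exceed it even when timing makes no difference. Participants are those who answered a digital letter and consented, so a departure from the national figure in either direction is plausible. The benchmark is also annual, while the last recruits have six months of follow-up at the interim, and the article does not say how the two are aligned. Adverse-event reporting is marked as not applicable, so this look is the main safety check that the article describes.

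**Follow-up.** The primary endpoint is binary with a 12-month window. A board that has seen the effect size may change the follow-up length, yet the endpoint has no room for a different length. Either the change does not touch the primary test, or the horizon of that test is chosen after seeing the data. A reader cannot tell which is meant.

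**Working it through.** **1. Reproduce the planning rate and sample size.**
- Events: 0.5 × 20,000 + 6,000 = 16,000. Rate: 16,000/178,000 = 8.99%, printed as 8.9%.
- Evening rate under ITT: 8.99% × (1 − 0.25 × 0.844) = 8.99% × 0.789 = 7.09%.
- Two-proportion formula, two-sided 0.05, 80% power, with continuity correction: 3,331 per arm, 6,662 in total. This equals the printed figure. Without the correction it is 6,452.

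So the safety benchmark is the annual rate of about 8.9% that drives the sample size.

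**2. Can the benchmark hide a difference?** Input: 10,013 randomized 1:1, about n = 5,006 per arm. The morning rates are assumptions. The 5.3% is 16,000/300,000, using 400,000 people with COPD less the quarter undiagnosed. The 6.7% is an intermediate value that the article does not give. The evening rate is set equal to the benchmark.

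Z = (pE − pM)/√[2p̄(1 − p̄)/n], with p̄ the mean of the two rates.

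| Morning | Evening | RR | Z, 12-month rates | Z, half the events |
|---|---|---|---|---|
| 5.3% | 8.9% | 1.68 | 0.036/0.00513 = 7.0 | 0.018/0.00370 = 4.9 |
| 6.7% | 8.9% | 1.33 | 0.022/0.00536 = 4.1 | 0.011/0.00387 = 2.8 |

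In both rows the evening arm agrees exactly with the presumption, while the between-arm Z is large.

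**3. Can the benchmark raise a false alarm?** The article names no test for this comparison. Assume a one-sample test of one arm against 8.9%, upward, one-sided 0.025.
- Standard error under the benchmark: √(0.089 × 0.911/5,006) = 0.00402. Alarm threshold: 0.089 + 1.96 × 0.00402 = 9.69%.
- If both arms truly run at 10%: standard error √(0.10 × 0.90/5,006) = 0.00424, and P(alarm) = 1 − Φ((0.0969 − 0.1000)/0.00424) = 1 − Φ(−0.73) = 77%.
- With the benchmark and the rates both halved (4.45% and 5.0%), the figure is 47%.

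**4. Type I error if the primary horizon moves with the data.** Let t be the interim information as a fraction of the 12-month total, and T the final information on the same scale (T = 1 with no extension). Given interim Z₁ = z under the null, the unadjusted two-sided final test rejects with probability

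A(z, T) = 1 − Φ[(1.96√T − z√t)/√(T − t)] + Φ[(−1.96√T − z√t)/√(T − t)].

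Averaging A over z ~ N(0,1), with T set by the extension rule, gives the type I error. The article gives neither t nor T. The assumed ranges are t = 0.5 to 0.9 and T = 1.25 to 2.

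| Rule for extending | Type I error |
|---|---|
| Never | 5.0% |
| Only when 1 < \|Z₁\| < 1.96 | 4.6% to 5.9% |
| Whenever \|Z₁\| < 1.96 | 5.3% to 7.0% |
| Worst case: at each z, whichever of T = 1 and the extended T rejects more often | 5.5% to 7.3% |

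**5. The follow-up passages side by side.** Treatment period, primary window and secondary window are all 12 months. The interim section lets follow-up duration be adjusted. For an event counted only within 12 months, month 13 onward contributes no events. The adjustment therefore has no effect on the primary test unless the window is changed too.

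**The case against.** **The concurrent comparison is already planned.** Z-scores for the primary endpoint and mortality are between-arm measures, and the board also sees the effect size. In the examples above it would see Z of about 4.9 and 2.8 even with half the events. This stands. A reader might infer that the morning arm is ignored and that harm would pass unseen, but the interim section does not support that. What remains is narrower: the one sentence that defines the safety assessment points to a different and weaker comparator.

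**Harm boundaries belong in the charter.** The board acts under a charter that is not shown, and numerical boundaries may sit there. This also stands, so their absence from the article is not part of this point.

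**The low morning rates are not established.** Eligibility requires current LAMA use, and the article deliberately divides by 178,000 LAMA users. True: 5.3% and 6.7% are illustrations. It is also not stated that the annual rate would be applied unscaled to shorter follow-up.

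**Type I error may not be inflated at all.** If the 12-month endpoint is analysed as written, extension leaves the primary test at 5%. Extending only on promising results can even lower the error. With no efficacy stop, the interim adds no extra chance of declaring success, so an unadjusted final 0.05 is not in itself an error. All of this stands. A reader might infer that false-positive inflation is certain. It is possible and modest, and needs the primary horizon itself to move. Blinded presentation of the data helps little, because masking arm labels does not hide the size of a difference.

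**Conclusion.** The point holds in two limited parts.

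1. **The stated safety comparator is poorly chosen.** A fixed national planning rate is named although a randomized control arm and between-arm Z-scores are available at the same look. It can agree with an evening arm whose relative risk is 1.33 to 1.68 (assumed morning rates 6.7% and 5.3%). It can also alarm about 77% of the time with no difference (both arms assumed at 10%, assumed one-sample test at one-sided 0.025).

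2. **The follow-up provision contradicts the fixed 12-month endpoint.** This rests on the text alone. The consequence for type I error is conditional: none if the primary analysis stays at 12 months, and about 4.6% to 7.3% if the horizon is moved after the effect size is seen, under the assumed interim information of 0.5 to 0.9 and extension to 1.25 to 2 times the total.

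Severity: should-fix. The planned Z-scores limit the practical safety risk and the possible inflation is modest, but both sentences are stated rules that should not stand as worded.

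**What to change.** (a) Reword the safety sentence so that safety is assessed by comparing evening with morning on the primary endpoint and mortality, using the Z-scores already planned. Keep the planning rate only as a check on the sample-size assumption.

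(b) Reconcile the interim section with *Trial design*, Table 1 and *Outcomes* by stating that the primary analysis is at 12 months whatever the interim shows. Any longer follow-up is then either labelled a secondary analysis or triggered only by the pooled, arm-blind event rate.

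Cost: wording in the protocol and the board's charter, with no new data or analyses. The downside is that the sponsor gives up extending the primary endpoint on the strength of the observed effect.

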### Methods for additional analyses (e.g., subgroup analyses)

Continuous baseline variables will be summarized using means, 95% confidence intervals, medians, and interquartile ranges according to distribution. Categorical variables will be compared using frequencies and proportions. All statistical tests will be two-sided, and *p*-values of <0.05 will be considered statistically significant.

### Methods in analysis to handle protocol non-adherence and any statistical methods to handle missing data

Secondary analyses will include mITT and per-protocol analyses to provide a comprehensive evaluation of the study outcomes. No data on the primary outcome will be missing as national registries will be used for outcome assessment. Only self-reported outcomes such as MRC and CAT can be expected to be missing. It will be assumed all missing data will be missing at random or completely at random to allow for multiple imputations. No imputed data will be presented in the baseline table.

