**Methods:**

Randomized controlled open-label trial. Persons aged 30 years or older with a once-daily LAMA prescription and a confirmed COPD diagnosis were recruited. Participants were randomized in a 1:1 ratio to either morning or evening LAMA administration. Complete follow-up for the primary outcome, hospitalization-requiring AECOPD, or death from all causes within 1 year was captured from the Danish National Health Register, as were patient-reported outcome assessments at 6 and 12 months.

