### Objectives

The main objective of this intervention and research protocol is to determine whether evening administration of LAMA, as opposed to morning administration, is superior for the occurrence of hospitalization-requiring AECOPD or death from all causes. The intervention will have the following secondary objectives: (1) moderate COPD exacerbations, (2) all-cause hospitalization, (3) intensive care unit (ICU) admission, (4) need for non-invasive ventilation, (5) all-cause mortality, (6) Short-Acting Beta-Agonist (SABA) use / pick up rate, and exploratory endpoints (1) change in COPD Assessment Test (CAT) score, (2) change in Medical Research Council (MRC) score, and (3) change in the “soundly sleeping” parameter of CAT.

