## Statistical methods

### Statistical methods for primary and secondary outcomes

The primary and all secondary outcomes will be analyzed using the intention-to-treat (ITT) approach, which encompasses the entire cohort of randomized participants in the study. Additionally, per-protocol analyses will be conducted for patients taking inhalation medication 6–7 days per week at the allocated administration time for the full duration of the study, along with modified ITT (mITT) analyses for those who have taken less than 6 days or more than 2 days per week for any amount of time. These analyses will be performed on both the primary and all secondary outcomes, providing a comprehensive evaluation of the study’s results.

The primary outcome (hospitalization-requiring AECOPD or death from all causes within 12) will be presented as a fraction with percentage and relative risk with a 95% confidence interval. The groups will be compared using a two-sided binomial test. The same principles will be applied to secondary binomial outcomes. For the SABA pick-up rate, the incidence rate and ratios will be calculated and presented (including 95% confidence intervals) and compared using the chi-squared test. Changes in CAT and MRC (respectively) will be reported as median differences with IQR and compared within and between groups with a paired two-sided Wilcoxon signed-rank test and an unpaired two-sided Wilcoxon rank-sum test. A subgroup analysis will be performed on the primary outcome with the following subgroups: adherence group (high adherence: ≥4–5 days per week of adherence), age (≥65 years), asthma overlap, coexisting heart failure, body mass index (>30 kg/), frequent exacerbator (>1 severe exacerbation within 12 months prior to baseline), and treatment with systemic beta-2 antagonist at baseline. A *p*-value of <0.05 will be considered significant.

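### Missing CAT and MRC scores are all assumed missing at random without separating death from non-response, and the planned rank tests give no between-group estimate with a confidence interval

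*Protocol article*

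**What the plan says.** The article expects gaps only in questionnaire data: "Only self-reported outcomes such as MRC and CAT can be expected to be missing". For these it gives one rule: "It will be assumed all missing data will be missing at random or completely at random to allow for multiple imputations" (Protocol article, *Methods in analysis to handle protocol non-adherence and any statistical methods to handle missing data*). That section makes no exception for any cause of missingness and does not mention deaths.

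The scores come from "patient-reported outcome assessments at 6 and 12 months" (Abstract, *Methods*), with a further questionnaire on day 1 (Table 4). Under *Objectives* they are "exploratory endpoints (1) change in COPD Assessment Test (CAT) score, (2) change in Medical Research Council (MRC) score". *Outcomes* and Table 3 also class them as exploratory. Table 2, whose title covers both secondary and exploratory endpoints, lists them too.

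Under *Statistical methods for primary and secondary outcomes*, changes in CAT and MRC are summarised by medians and interquartile ranges and "compared within and between groups with a paired two-sided Wilcoxon signed-rank test and an unpaired two-sided Wilcoxon rank-sum test". The same section specifies 95% confidence intervals for the primary relative risk and the SABA rate ratio, but none for CAT or MRC.

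Death is an expected, recorded event. *Outcomes* states: "The primary efficacy endpoint is the occurrence of hospitalization requiring AECOPD or death from all causes within 12 months". All-cause mortality is also a secondary endpoint, defined in Table 2 as "Participant registered as dead in the CPR register".

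**The concern.** A score that was not returned by a living participant exists but is unknown. A score for a participant who has died does not exist. Missing at random describes only the first case. A rule that covers all missing scores puts the two together, and an imputation model fitted to survivors would give the dead survivor-like values. The wording also adopts the assumption because the method needs it, not because it has been argued.

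Non-response among the living raises a related issue. A participant recovering from a severe exacerbation may score worse and may also be less likely to answer. The trial hypothesizes that evening dosing changes the frequency of such events. Missing completely at random is then hard to defend. Missing at random is plausible only if the imputation model contains those post-randomization events.

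The stated analysis would also leave the reader without a usable result. A rank-sum p-value with medians and interquartile ranges does not say how large the difference between the arms is or how precisely it is known. A within-group signed-rank test describes change over time in one arm, which includes natural course and regression to the mean, and does not compare the arms.

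**Working it through.** The article gives no power calculation, standard deviation or expected response rate for CAT or MRC, so there is no planned figure for these endpoints to reproduce. The stated sample size of 6,662 concerns the primary outcome only. The nearest figure is the planned annual risk under *Sample size*: 16,000/178,000 = 8.99%, printed as 8.9%.

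**1. How many 12-month scores would be absent because of death?** *Sample size* states that each year "there are approximately 20,000 admissions with AECOPD (severe AECOPD) and 6,000 deaths in patients with COPD". It also gives 178,000 LAMA users and about 400,000 people with COPD, a quarter of them undiagnosed, so about 300,000 diagnosed. The number randomized is 10,013 (Abstract). Expected deaths = 6,000 / denominator × 10,013.

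| Denominator | Annual mortality | Deaths among 10,013 |
|---|---|---|
| 178,000 LAMA users | 3.4% | 338 |
| 300,000 diagnosed | 2.0% | 200 |
| 400,000 all COPD | 1.5% | 150 |

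The first row is an upper figure, because the 6,000 deaths are among all COPD patients and not only LAMA users. Mortality among volunteers may differ from all three rows.

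**2. How far could deaths alone move the comparison?** Take the upper mortality, 3.37%, and assume the printed 21.3% relative reduction applies fully to deaths. The arms then differ by 3.37% × 0.213 = 0.72 percentage points in mortality.

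- If each imputed score for a dead participant were wrong by 10 CAT points (an assumed value), the mean contrast would shift by 10 × 0.0072 = 0.07 points.
- If deaths were ranked worst and survivors did not differ, the Mann-Whitney probability would be 0.5 + (0.0337 − 0.0265)/2 = 0.5036. With n = 5,006 per arm, its standard error is √[(2n+1)/(12n²)] = 0.0058, so z = 0.62.

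Both effects are small.

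**3. How many participants have an event that could drive non-response?** At 8.9% in both arms, 0.089 × 10,013 ≈ 890 would have a primary event. If the planned effect occurs, the evening rate is 0.089 × 0.787 = 7.0%, the average is about 7.95%, and about 800 have an event. These counts include the deaths. The article gives no non-response rate, so the resulting bias cannot be sized.

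**4. Can a rank-sum test be combined with multiple imputation?** A simulation used assumed values: 500 per arm, baseline SD 7, change SD 5, about 27% missing at random, 20 imputations, no effect, 2,000 runs. The Mann-Whitney probability and its variance were pooled by Rubin's rules. The type I error was 4.8% against a nominal 5%, with simulation error √(0.05 × 0.95/2,000) ≈ 0.5 percentage points. The combination works.

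**5. What does baseline adjustment offer?** For means with equal variances at both times, the variance of ANCOVA relative to a change-score analysis is (1 − r²)/[2(1 − r)] = (1 + r)/2. That is 0.80 at r = 0.6 and 0.85 at r = 0.7, a reduction of 20% and 15%. The correlations are assumed. The comparator is a mean change score and not the planned Wilcoxon test, so the figure does not measure a loss from the plan as written.

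**The case against.** The strongest reply has four parts.

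*The detail may be elsewhere.* The article condenses a full protocol and may have a separate analysis plan. That holds for the pooling rule. A reader might infer that Wilcoxon tests and multiple imputation cannot be used together. The documents do not support this: nothing in them rules out pooling, and step 4 shows that a valid route exists. The reply does not hold for the missing-data rule itself, which the article states for all missing data without exception.

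*The endpoints are exploratory and the deaths are few.* This stands, and it limits the weight of the point. The primary outcome and the registry-based secondary outcomes do not depend on the questionnaires.

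*The planned test is valid.* A rank-sum test on change is protected by randomization, and a median MRC change of zero in both arms would not make it insensitive. Without covariates, a proportional-odds model leads to essentially the same test. All of this stands. The gap is the absence of an estimate with an interval, not the validity of the p-value.

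*The within-group tests are additional.* The between-group test is also specified, so the randomized contrast is tested. That is correct, but the within-group tests add nothing to it and can be misread as evidence of effect.

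**Conclusion.** The point stands in a limited form. The article's rule treats every missing CAT or MRC score as missing at random or completely at random and does not distinguish death from non-response. Followed to the letter, it would create 12-month scores for about 150 to 338 of 10,013 participants (1.5% to 3.4%). That range rests on the article's national counts applied to the trial population. The stated analysis then gives an unadjusted rank comparison with no between-group estimate and confidence interval, although a change score presupposes a baseline score.

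A reader might go further and infer that the trial intends to invent scores for the dead. The article does not say so. This is an inference from the word *all*, and the supportable statement is that the rule does not exclude it. Nor should 338 be quoted alone, since it is the top of the range.

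Under the assumptions in step 2, bias from deaths alone is probably small. Bias from event-related non-response cannot be sized from the article. The primary conclusion of the trial is unaffected.

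**What to change.** In the missing-data section, separate death from non-response:

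- Impute CAT and MRC only for participants alive at the visit, separately by arm, with registry events since randomization in the imputation model.
- State how deaths are handled: scores while alive as the main analysis, with a worst-rank analysis as sensitivity.
- Add one delta-shift analysis that departs from missing at random.

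In the statistical methods section, report a baseline-adjusted between-group effect with a 95% confidence interval: ANCOVA or a repeated-measures model over 6 and 12 months for CAT, and proportional odds for MRC and the CAT sleep item. Pool by Rubin's rules and drop the within-group tests.

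The cost is a few sentences and a little programming. The death register, registry events and questionnaires are already part of data collection. The price is a model assumption (linearity, or proportional odds) that the rank test does not need.
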